## Electroacupuncture

Participants allocated to the electroacupuncture group will receive treatment with needles inserted at previously designated points. Based on preliminary tests, the research group developed an acupoint matching scheme. The acupoints include bilateral Feishu (BL13), Pishu (BL20), Shenshu (BL23), Hegu (LI4), Zusanli (ST36), Sanyinjiao (SP6) and Taichong (LR3). All acupoints are localized according to the WHO Standard Acupuncture Locations and are shown in Table 2 and Fig. 3. All needles must achieve De qi (a sensation including soreness, numbness, distention, and heaviness), which is believed to be an essential component for acupuncture efficacy. After De qi, unilateral Feishu-Shenshu and Sanyinjiao-Taichong points will be used as the connection points of electroacupuncture. The density wave will be at a frequency of 2 Hz/100 Hz, and the current intensity will be in the range of 0.1~1.0 mA (according to the participant's comfort). A single session will last 30 min/day; 6 sessions will constitute a course of treatment, with 1 day of rest between courses; and the intervention will continue for 4 courses.

**Table 2 Tab2:** Locations of acupoints in electroacupuncture group

Acupoints	Locations^a^
Feishu (BL13)	On the back, under the spinous process of the 3rd thoracic vertebra, 1.5 cun laterally
Pishu (BL20)	On the back, under the spinous process of the 11th thoracic vertebra, 1.5 cun laterally
Shenshu (BL23)	On the back, under the spinous process of the 2nd lumbar vertebra, 1.5 cun beside the posterior midline
Hegu (LI4)	Between the 1st and 2nd metacarpal bones
Zusanli (ST36)	3 cun directly below Dubi, and one finger-breadth lateral to the anterior border of the tibia
Sanyinjiao (SP6)	Posterior to the mesial border of the tibia, and 3 cun above the tip of the medial malleolus
Taichong (LR3)	In the depression anterior to the junction of 1st and 2nd metatarsal bones

^a^1 cun (≈ 20 mm) is defined as the width of the interphalangeal joint of the volunteer’s thumb

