## Sham electroacupuncture

Participants in the sham electroacupuncture group will receive treatment using blunt needles at the designated acupoints. Blunt needles have the appearance of real needles, but they do not penetrate the skin. The sham electroacupuncture group will receive treatment without needle manipulation for De qi, which is characterized by soreness, numbness, heaviness and a feeling of pressure. Non-acupoints are different from real acupoints or meridians and are shown in Table 3 and Fig. 3.

**Table 3 Tab3:** Locations of non-acupoints in sham-electroacupuncture group

Acupoints	Locations
Beside Feishu	1 cun^a^ beside Feishu (≈ 20 mm)
Beside Pishu	1 cun beside Pishu (≈ 20 mm)
Beside Shenshu	1 cun beside Shenshu (≈ 20 mm)
Beside Hegu	1 cun before Hegu (≈ 20 mm)
Beside Zusanli	1 cun backward Zusanli (≈ 20 mm)
Beside Sanyinjiao	1 cun backward Sanyinjiao (≈ 20 mm)
Beside Taichong	1 cun backward Taichong (≈ 20 mm)

^a^1 cun (≈ 20 mm) is defined as the width of the interphalangeal joint of volunteer’s thumb

The sham electroacupuncture procedure is as follows: the wire to the electroacupuncture instrument is cut off before the intervention. After the acupuncture procedure is completed, the non-acupoints are connected with electroacupuncture, and the parameters and course of treatment will be the same as those in the electroacupuncture group.

Considering ethical factors involved in this sham treatment, we will offer free acupuncture treatment and compensation to participants in the sham electroacupuncture group after all the conclusion of the trial.

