#### Neurophysiological index

The SCV of the bilateral superficial peroneal nerve will be measured by EMG. CPT will be performed at 2000 Hz, 250 Hz and 5 Hz, and for each group, the CPT values on the dorsal side of the first bilateral toe will be measured. The Short-Form McGill Pain Scale will be used to evaluate the subjective pain experienced by the subjects in each group. Multiple regression analysis will be performed to analyse the correlation between the SCV, CPT, McGill Pain Scale values and the multimodal cerebral imaging results to reveal and verify the relationship between the degree of peripheral neuropathy, subjective pain and the changes in cerebral function in participants with PDPN.

Based on the above results, the SCV of the bilateral superficial peroneal nerve, the CPT value of the dorsal side of the first toe and the Short-Form McGill Pain Scale will be recorded and evaluated in participants with PDPN after each electroacupuncture and sham electroacupuncture treatment. We will continue to use the method of multiple regression analysis to analyse the correlation between the SCV, CPT, McGill Pain Scale values and the results of the multimodal cerebral imaging to study the relationship between the clinical therapeutic effect of electroacupuncture and the improvement of cerebral central sensitization and reveal the mechanism of electroacupuncture in the treatment of PDPN.

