#### Short-Form McGill Pain Questionnaire

The Short-Form McGill Pain Questionnaire is a high-quality tool used to evaluate neuropathic and nonneuropathic pain conditions [29]. It provides basic information for pain research. The questionnaire will be administered at baseline, the 1st, 2nd, 3rd and 4th weeks of the treatment period, and at the 1-, 2-, 3- and 6-month follow-ups after treatment.

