### rs-fMRI data acquisition

The rs-fMRI scan will be collected with a 3.0 Tesla superconductor (Skyra, Siemens, Erlangen, Germany) in Guang’anmen Hospital. Participants will undergo rs-fMRI scans at baseline and after the 4th week of treatment. Before the scan, participants will be asked to wear earplugs and remove all metal objects from their bodies. Relevant regulations and procedures of the MRI room will be strictly observed. Using foam pads to reduce head movement, participants will be required to remain supine and awake during the entire scan.

Whole cerebral function imaging adopts a T2-weighted echo planar imaging (EPI) sequence for axial scanning, taking the mid-sagittal parallel connection (AC-PC) as the positioning line. Scanning parameters are as follows: number of layers 47, repetition time (TR) = 3000 ms, echo time = 30 ms, layer thickness = 3.0 mm, field of view (FOV) =220 mm × 220 mm, flip angle = 85°, size of voxel = 3.0 mm × 3.0 mm, in-plane resolution = 64 × 64, phase resolution = 100%, and data collection time = 12:30s.

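### The timing of SCV, CPT and McGill is inconsistent and sets no interval from a session; read literally, CPT could pick up an acute local effect in the electroacupuncture arm only

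*Protocol article*

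**What the plan says.** The Neurophysiological index section, under Primary outcomes, names three measures for participants with PDPN.

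- **SCV:** "The SCV of the bilateral superficial peroneal nerve will be measured by EMG".
- **CPT:** at 2000, 250 and 5 Hz; "the CPT values on the dorsal side of the first bilateral toe will be measured".
- **Short-Form McGill:** subjective pain.

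Its second paragraph says that these "will be recorded and evaluated in participants with PDPN after each electroacupuncture and sham electroacupuncture treatment". No interval between session and measurement is given, and that paragraph mentions the first toe without saying which side. It is the only on-treatment timing for SCV and CPT in the text; the study schedule (Fig. 2) is not shown.

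Other sections give different timings. The opening of Primary outcomes speaks only of measurement before and after acupuncture treatment. The Short-Form McGill Pain Questionnaire section says "The questionnaire will be administered at baseline, the 1st, 2nd, 3rd and 4th weeks of the treatment period", followed by visits at 1, 2, 3 and 6 months. The rs-fMRI data acquisition section says "Participants will undergo rs-fMRI scans at baseline and after the 4th week of treatment".

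On exposure, the Electroacupuncture section requires De qi, which it defines to include numbness, at all needles. It then says that "unilateral Feishu-Shenshu and Sanyinjiao-Taichong points will be used as the connection points of electroacupuncture", in sessions of 30 minutes. The Sham electroacupuncture section uses blunt needles that do not penetrate, seeks no De qi, and says that "the wire to the electroacupuncture instrument is cut off before the intervention".

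**The concern.** CPT is a sensory threshold to electric current. Table 2 places Taichong at the first and second metatarsals, in the same region of the foot as the dorsal first toe where CPT is read. If CPT is taken soon after a session, the EA arm has just had local needling with De qi and, on one side, current; the sham arm has had neither. The baseline reading has no preceding exposure in either arm. An EA-sham difference in CPT change could then be an acute local sensory effect, a change in neuropathy, or both. Analysis could not separate them, because the exposure coincides with the arm.

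This matters because the degree of neuropathy and its correlation with brain state are the stated primary goal, and CPT is one of the measures entering that correlation. The conflicting timings also leave open which clinical reading belongs with the second scan. For the McGill, the point is the contradictory schedule.

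**Working it through.** The plan gives no figure for this point, so there is none to reproduce. The check sets the sections side by side and then illustrates a possible size.

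**1. Timing**

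| Section | Measures | Timing |
|---|---|---|
| Primary outcomes, opening | neuropathy, pain | before and after treatment |
| Neurophysiological index | SCV, CPT, McGill | after each EA or sham treatment, no interval |
| Short-Form McGill | McGill | baseline, weeks 1 to 4, then 1, 2, 3 and 6 months |
| rs-fMRI data acquisition | scan | baseline and after week 4 |

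Random allocation gives 24 sessions per participant (6 × 4) and 60 PDPN participants. Taken literally, the second row means 60 × 24 = 1,440 assessment rounds, with 1,440 × 3 frequencies × 2 sides = 8,640 CPT readings. Weekly assessment would be 60 × 4 = 240 rounds, and one post-course assessment 60. The rows cannot all hold for the McGill. No stated analysis uses a session-by-session SCV or CPT course.

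**2. Exposure near the CPT site, by arm**

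| | EA | Sham |
|---|---|---|
| Penetrating needle at Taichong | yes, both feet | no |
| De qi sought | yes | no |
| Current at Taichong | one side, 30 min | none |

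**3. Illustrative size for CPT**

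Assumptions, none from the documents: no lasting change in either arm, a transient shift of d SD in EA only, and a two-sided 5% t test. The article's 30 per arm gives 58 degrees of freedom and a critical value of 2.002.

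- *Stimulated foot only.* Noncentrality λ = d × √(n/2) = d × √15 = 3.873d.
- *Mean of both feet, one shifted.* The mean moves by d/2. With between-foot correlation 0.7, its SD is √((1 + 0.7)/2) = √0.85 = 0.922. The effective shift is (d/2)/0.922, and λ is 3.873 times that.

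| d | λ, one foot | P(reject) | effective shift, mean of feet | λ | P(reject) |
|---|---|---|---|---|---|
| 0.3 | 1.162 | 21% | 0.163 | 0.630 | 10% |
| 0.5 | 1.936 | 48% | 0.271 | 1.050 | 18% |
| 0.8 | 3.098 | 86% | 0.434 | 1.680 | 38% |

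The nominal rate is 5%. A normal approximation gives 21%, 49% and 87%, and 10%, 18% and 39%. With 24 per arm, the number before the attrition allowance, the t test on the stimulated foot gives 17%, 40% and 77%.

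**The case against.** The strongest reply is that the sentence is ambiguous. It can mean after the course of treatment in each arm. That reading fits the before-and-after wording of the primary goal, the two scans, and the planned correlation with imaging change values. On it there are no 24 readings. The schedule figure, where visit timing would normally appear, is not available. This stands, so the literal reading cannot be taken as fact. It does not remove the point: the course reading still sets no interval from the last session and still disagrees with the McGill schedule.

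Second, the text says after and never immediately after; closeness in time is inferred. This also stands, and it is why the missing interval is the thing to fix.

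Third, current is unilateral while CPT is bilateral, so at most one foot carries current and averaging dilutes the effect. This stands for current and is why both sets of figures are shown. It is weaker for needling, since De qi is sought in both feet.

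Fourth, both the existence and the size of a transient shift are assumed. The calculation shows only how often a t test would pick up a shift that is put in. It says nothing about the size of any bias in the correlation with imaging.

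A reader might go further and infer that SCV and McGill carry the same local effect. The documents do not support that: the argument concerns a current threshold read near a stimulated foot point, no mechanism is shown for SCV, and the McGill has visits months clear of any session.

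**Conclusion.** The timing of these measures needs reconciling, and as written it permits an avoidable ambiguity in CPT, an index listed under Primary outcomes. That the sections disagree, that no interval is set, and that only the EA arm has De qi needling and current near the CPT site all follow from the text. That CPT would actually shift is an assumption. Over the assumed 0.3 to 0.8 SD, the chance of a spurious arm difference runs from 21% to 86% on the stimulated foot, and from about 10% to 38% for the mean of both feet at an assumed between-foot correlation of 0.7.

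A reader might conclude that the EA-sham comparison, or the correlation with imaging, is known to be biased. The documents do not support that: they give no estimate of a local effect, and the sentence allows the whole-course reading. This is a worthwhile, inexpensive improvement held with moderate confidence, not a demonstrated flaw in the trial's main result.

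**What to change.** Reconcile the opening of Primary outcomes, the Neurophysiological index section and the Short-Form McGill section. In the Neurophysiological index section, replace the after-each-treatment wording with the following:

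- SCV, CPT and McGill at baseline and at one post-course assessment paired with the second scan.
- That assessment not directly after a session, for example on a non-treatment day, with the same interval from the last session in EA and sham.
- The side or sides analysed for CPT and SCV stated.
- Those values named as the ones entering the correlation and regression.

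Keep the weekly and follow-up schedule for the other McGill assessments. The treatment itself is unchanged.

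The cost is a change of wording and coordination of the assessment with the scan visit. Any session-by-session SCV and CPT course would be lost. On the literal reading, post-baseline rounds fall from 1,440 to 60.

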**Method and design:**

This will be a randomized controlled trial. A total of 150 participants will be recruited and assigned to one of three groups: the healthy group, the DM without PDPN group and the DM with PDPN group. Participants in the DM without PDPN and the DM with PDPN groups will each be further divided between an electroacupuncture group and a sham electroacupuncture group. Participants will receive six treatment sessions per week for 4 weeks. Multimodal cerebral imaging includes resting-state functional magnetic resonance imaging (rs-fMRI), diffusion tensor imaging (DTI) and magnetic resonance spectroscopy (MRS); this neurophysiological testing will be the primary outcome measure. Subjective pain scales and blood analysis will be a secondary outcome measure and will be used to assess the clinical efficacy of the intervention. Multimodal cerebral imaging will be used to detect cerebral activity changes in each treatment group. The clinical data and fMRI data will be analysed for all the groups. Multiple correlation regression analyses will be used to assess the association between changes in cerebral functional activity and the improvement of clinical outcomes after acupuncture treatment.

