## Outcomes

### Primary outcomes

The primary goal of this study is to observe the degree of peripheral neuropathy and measure the subjective pain perceptions in participants with PDPN before and after acupuncture treatment and assess their correlation with the characteristics of the central sensitization state of the brain. We will measure the sensory nerve conduction velocity (SCV) and the current perception threshold (CPT) and will use the McGill Pain Scale while also combining multimodal brain imaging data for our correlation analysis.

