## Statistical analysis

### Neuroimaging data analysis

Cerebral imaging testing will be entrusted to a third party, professionals of the independent neuroimaging research laboratory at Martinos Center for Biomedical Imaging, Massachusetts General Hospital, Harvard Medical School, USA, for statistical analysis. (1) fMRI data preprocessing: We will use SPM12 for slice timing correction (SPM12, http://www.fil.ion.ucl.ac.uk/spm/), rigid body correction for head motion with the FSL (https://fsl.fmrib.ox.ac.uk/fsl/fslwiki/) [33, 34], subjects with head movement < 1 mm and a rotational shift of < 2° will be entered into the subsequent analysis, bandpass temporal filtering (0.01–0.08 Hz), whole brain signal regression and ventricular and white matter signal regression. We will use the FreeSurfer version 6.0.0 software package to process the structural data and surface mesh representations of the cortex from each participant’s images [35]. Images will be reconstructed and registered to a common spherical coordinate system; functional images will be coregistered to anatomical images and normalized to the MNI152 standard template. (2) Morphological analysis of the grey matter structure of the brain: surface-based morphometry (SBM), voxel-based morphometry (VBM) and morphological analysis of subcortical grey matter structures in the grey matter of the brain will be based on anatomical data. The CIVET-pipeline toolkit and SurfStat software in the MATLAB environment will be used for the processing and statistical analysis of the image data. (3) Analysis of white matter parameters of the brain: Based on DTI scanning, the voxel-based analysis method will be used to process and analyse the test data using the MATLAB toolkit PANDA software. Image processing will include converting images from DICOM format to NIfTI format, eliminating extracerebral tissue and clip aligned images, eddy current correction and realignment, image normalization, calculating tensor and colour maps and fibre tracking and visualization. Finally, FSL software will be used to present the data, and the corresponding white matter fibre bundles will be identified according to the core white matter map of Johns Hopkins University. (4) Brain metabolite analysis: Based on the MRS scanning, images will be converted from DICOM format to RDA format, RDA data will be imported into the LC Model software, GAMMA software will be used in the same sequence and with the same parameters, the absolute concentration of each substance in the imported data will be calculated, and the substance concentration with SD < 15% will be imported into the SPSS 26.0 software package and analysed according to statistical principles. (5) Correlation analysis of SCV, CPT, McGill and multimodal brain imaging research data: Pearson linear correlation analysis in the SPSS 26.0 package will be used to correlate clinical effect indicators such as SCV, CPT and McGill values with the change values from multimodal brain images. The statistical threshold will be set as *P* < 0.05, a Pearson correlation coefficient of *r* > 0 will indicate a positive correlation, and *r* < 0 will indicate a negative correlation. According to the results of the correlation analysis, multiple regression analysis or principal component analysis will be carried out to deeply explore the brain function change characteristics and pathogenesis of brain central sensitization in PDPN.

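### An electroacupuncture mechanism is to be read from a correlation of clinical and imaging measures that names no treatment arm and is not tied to any comparison with sham

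*Protocol article*

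**What the plan says.** The Primary outcomes section makes the correlation part of the primary goal: clinical measures are taken before and after treatment in PDPN in order to "assess their correlation with the characteristics of the central sensitization state of the brain".

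Under Neurophysiological index, sensory conduction velocity (SCV), current perception threshold (CPT) and McGill scores are "evaluated in participants with PDPN after each electroacupuncture and sham electroacupuncture treatment", so both randomised arms are measured. The method follows: "We will continue to use the method of multiple regression analysis to analyse the correlation between the SCV, CPT, McGill Pain Scale values" and the imaging results. The stated purpose is to "study the relationship between the clinical therapeutic effect of electroacupuncture and the improvement of cerebral central sensitization and reveal the mechanism of electroacupuncture".

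Item (5) of Neuroimaging data analysis gives the test. Pearson correlation will "correlate clinical effect indicators such as SCV, CPT and McGill values with the change values from multimodal brain images", and "The statistical threshold will be set as *P* < 0.05". Multiple regression or principal component analysis may follow. The abstract describes the same analysis as one to "assess the association between changes in cerebral functional activity and the improvement of clinical outcomes after acupuncture treatment".

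None of these places names arm as a term, states an interaction with arm, or says whether the EA and sham arms are pooled or analysed separately.

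Arm comparisons do appear elsewhere:
- The third objective in Background calls for a controlled EA-versus-sham study.
- The abstract mentions cerebral changes in each treatment group.
- Clinical data analysis has an ANOVA of between-group changes, but for clinical data.
- The comparison spelled out under Cerebral imaging index is PDPN against non-PDPN.

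**The concern.** A correlation between two changes measured after randomisation does not show that the treatment caused either one. Pain, nerve and brain measures may move together in sham-treated patients because of natural course, expectation or background medication. (Table 1, item 4a, lists conventional drugs including analgesia.) The randomised sham arm is there to remove such explanations, but the analysis that leads to the mechanism conclusion is not said to use it.

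What is at stake is the main mechanistic statement of the trial. As worded, the article has no step that separates two situations: EA acting on pain through the brain, and pain and brain measures varying together whatever the treatment. This holds for a single correlation chosen in advance, so it is not a multiplicity problem.

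**Working it through.** **Inputs from the article.** PDPN participants: 30 EA and 30 sham (Random allocation). Attrition 20%, so 24 per arm remain: 30 × 0.8 = 24 (Sample size calculation). Threshold 0.05, taken as two-sided because both signs of r are interpreted. The article gives no error rate or power for the correlation, so there is no figure of its own to reproduce.

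**Assumptions, not in the article.** Natural within-arm correlation ρ between clinical change and imaging change: 0 to 0.5. EA-minus-sham shift d, in SD units: 0 to 1.5. Changes are bivariate normal and treated as already baseline-adjusted.

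**Test.** t = r√(n − 2)/√(1 − r²). It is significant when |r| exceeds 0.254 (n = 60), 0.285 (n = 48) or 0.361 (n = 30).

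**Step 1: EA identical to sham (d = 0).** Share of simulated trials with a significant correlation (20,000 to 40,000 per cell; repeat runs differ by about one percentage point):

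| ρ | Pooled, n = 60 | Pooled, n = 48 | One arm, n = 30 |
|---|---|---|---|
| 0 | 5% | 5% | 5% |
| 0.2 | 33% | 28% | 18% |
| 0.3 | 66% | 55% | 37% |
| 0.4 | 90% | 82% | 61% |
| 0.5 | 99% | 96% | 83% |

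A t test of EA against sham on the imaging change stays near 5% at every ρ.

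**Step 2: what a real EA effect does to the correlation.** Within one arm, or after adjustment for arm, a mean shift leaves r unchanged. At ρ = 0.3 and d = 0.81 on both measures, the single-arm rate is 37% with or without the effect, and the arm-adjusted rate is 65% with or without it.

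With 1:1 arms pooled and both measures shifted by d, the correlation becomes (ρ + d²/4)/(1 + d²/4).
- ρ = 0.3, d = 0.81: d²/4 = 0.164, so (0.3 + 0.164)/1.164 = 0.40. The rate rises from 66% to 90%.
- ρ = 0, d = 0.81: 0.164/1.164 = 0.14. The rate is 19%.
- ρ = 0, d = 1.0: 0.25/1.25 = 0.20. The rate is about 34%.
- ρ = 0, d = 1.5: 0.5625/1.5625 = 0.36. The rate is 85%.

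In the last three cases nothing links the two measures within an arm. The pooled correlation comes only from the two arm means lying apart.

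**Step 3: candidate decision rules, 30 per arm.** Criterion (a) is an EA–sham difference in imaging change, (b) an EA–sham difference in the paired clinical change, and (c) an association after adjustment for arm, each at 0.05.

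| True state | (a) and (c) | (a), (b) and (c) |
|---|---|---|
| No effect on either, ρ = 0.5 | 5% | 1% |
| Imaging shifted 0.8 SD, pain not at all, ρ = 0.5 | 85% | 4% |
| Both shifted 0.8 SD, ρ = 0.5 | 84% | 76% |
| Both shifted 0.8 SD, ρ = 0.3 | 55% | 49% |

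Criteria (a) and (c) alone would still claim a pain mechanism when pain is unaffected, so (b) is needed. With 24 per arm, all three are met in about 62% (ρ = 0.5) and 33% (ρ = 0.3) when both measures shift by 0.8 SD.

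**The case against.** Four points can be made for the protocol.

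1. **A condensed article need not list covariates.** The sentence on the EA mechanism names multiple regression, and the missing covariate list alone is no fault. The unadjusted Pearson threshold stands in another section, whose stated aim is the pathogenesis of central sensitisation in PDPN. The decision rule simulated here is therefore put together from two places, and nowhere does the article say that one significant r proves a mechanism. This stands as a limit on the figures. It does not remove the point, because the article states both the method and the conclusion drawn from it.

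2. **Arm comparisons exist.** A reader might infer that the plan has no EA–sham comparison, or that a mechanism would be declared even if EA did nothing for pain. The documents do not support that: Background, the abstract and Clinical data analysis all refer to group comparisons. What remains is that none of them is made a condition of the mechanism conclusion, and the ANOVA is placed under clinical data.

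3. **The correlation is not blind to a real effect.** A reader might infer that it is significant just as often when EA equals sham as when EA works. That is exact only within an arm or after adjustment for arm. If arms are pooled, which the text leaves open, a real effect on both measures raises the rate (66% to 90% at ρ = 0.3). The information is non-specific, however, since pooling also creates correlation with no within-arm link.

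4. **The correlations are assumed.** At ρ = 0 the rate is the nominal 5%, and at 0.2 it is a third or less. The high figures need ρ of 0.3 or more.

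**Conclusion.** The point holds in this form: the mechanism conclusion rests on an association that names no arm and is not tied to any EA-versus-sham contrast, and that association can be significant with high probability when EA equals sham. The size depends on an unknown natural correlation. From 0 to 0.5 the rate runs from 5% to 99% with 60 pooled participants and from 5% to 83% in a single arm of 30. These figures describe one two-sided Pearson test under normality, not the full regression, whose terms are not given. The fault lies in the stated inference; the data collection is sound. It should be corrected before the data are analysed, because the correlation is part of the primary goal.

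**What to change.** In Neurophysiological index and in item (5) of Neuroimaging data analysis:

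- State whether arms are pooled, and include arm in the association model among randomised PDPN participants.
- Claim an EA mechanism for a pre-specified imaging measure only if (a) its baseline-adjusted change differs between EA and sham, (b) the baseline-adjusted change in the paired clinical measure also differs between EA and sham, and (c) the association holds after adjustment for arm.
- Even then, word the result as consistent with mediation, because the link between imaging change and clinical change is not itself randomised.
- Otherwise report the correlations as association only, and remove the statement that this analysis shows how electroacupuncture works.

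The cost is revised wording and a few extra models on data already planned. The downside is that fewer results will qualify as mechanism, as the last column of the second table shows, and fewer still after attrition.
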